### Patient Focus Groups and Semistructured Interviews

To complement the quantitative data collection, focus group discussions or semistructured interviews will be held at the completion of the health behavior change support program. The participants of the health behavior change support program will be invited to participate in focus groups or semistructured interviews. This will allow a detailed examination of the behavior change intervention experience from the participant’s perspective. The patients who were recalled to their practice for a “heart and stroke check”, who did not attend the practice for the check, will also be invited to participate in semistructured interviews to examine the reasons for their nonattendance, and their experience of receiving the recall letter. The focus group sessions or interviews will be conducted until the saturation of themes is achieved, that is, no new major themes are detected.

### System Related Data- Case Study of HeartLink

Multiple data sources will be used to examine the complex range of system-related issues in the case study.

### Focus Groups, Semistructured Interviews, and Key Informant Forum

The focus group discussions or semistructured interviews will be conducted with key stakeholder groups over the course of the study, including with general practice staff, Lifestyle Advisors, allied health professionals, and community-based lifestyle modification program providers. These discussions will aim to identify themes in relation to the research questions, and will also provide an opportunity to engage key individuals and groups in the intervention process. Purposive sampling will be used to ensure key informants in each stakeholder group are represented. The goal will be to recruit at least eight people for each of the focus groups. The topic guides will be developed using key issues identified from the literature, including the critical success factors for systems thinking in prevention of chronic disease, and key constructs for understanding implementation of complex interventions [37,19].

The topic guides will provide an initial direction for the discussions. A forum with key policy and program informants from the primary health care sector will be conducted near the completion of the *HeartLink* intervention to gain feedback on the policy and program implications of the findings, and to provide input into the emergent CVD prevention model.

An open-ended questionnaire will be used to gather the views of the key informants.

### Primary Health Care and Chronic Disease Prevention Policy and Program Documents

Document analysis is commonly used in case study research as an additional source of evidence, and as a means of triangulation [22]. The key national and local primary health care and chronic disease prevention policy documents will be examined. The documents reviewed will include the National Primary Care Strategy, the National Primary Health Care Strategic Framework, and the National Prevention Taskforce’s National Preventative Health Strategy [38-40]. This analysis aims to provide information on the macro and meso-systems context in which the *HeartLink* intervention is occurring, provide a means of tracking change in relevant issues over the intervention period, and to verify findings or corroborate other evidence collected as part of the study [41].

### Reflective Diaries of Lifestyle Advisors

Lifestyle Advisors will keep reflective diaries for the duration of the *HeartLink* intervention. The role of the advisor is similar to that of the “boundary spanner”, as described by Etz, providing a connection between the general practice and community sector, thus offering insight into the linkage process between the sectors [42]. The advisors will be encouraged to record issues related to patients, the general practice, and their work with community lifestyle modification providers. They will be also encouraged to reflect on their own practice, and will be given a set of prompt questions encouraging them to consider barriers, enablers, opportunities, and threats for the future implementation of the intervention approach. The diaries will be reviewed regularly to ensure data quality, and will be collected at the completion of the intervention.

### Intervention Process Measures

The system’s outcomes will be further examined using a range of process measures. One of which is a brief audit to assess the degree of implementation of the CVD prevention system elements by each stakeholder group. A specific audit tool will be developed for the three key stakeholder groups: (1) general practice, (2) community-based allied health professionals, and (3) other lifestyle modification program providers based on the Assessment of Chronic Illness Care tool [43].

### Data Analysis

#### Quantitative Data Analysis

Changes in the CVAR will be reported at the total practice population level, but also analyzed by each practice. The primary analysis will be done on an Intention to Treat basis. The CVAR was chosen as the primary health outcome, as it represents an all around measure of the *HeartLink* intervention’s ability to meet its objectives.

An analysis of the quantitative data collected from the clinical data and the participant survey will be undertaken. Univariate comparisons between the pre and post intervention groups will be conducted using a chi-square test for equal proportion (or Fisher’s exact tests where numbers are small), and reported as numbers and percentages. Continuous normally distributed variables will be compared using student’s *t* tests and reported as means (95% confidence interval). Nonnormally distributed data will be compared using Wilcoxon signed rank tests.

The *HeartLink* pilot data will be used to estimate population proportions (and confidence intervals) for those at high risk of CVD in the ACT. This data will also generate planning information for a future larger study. The intercluster correlation coefficient, effect size, and standard deviation will be examined to help determine sample size calculations, cluster size, and number of clusters.

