### The Model for Prevention Study

The MoFoP study aims to investigate a whole-of-system approach to the prevention of CVD in the primary health care setting. The MoFoP study will examine the *HeartLink* CVD risk reduction intervention in primary health care. The study will identify key elements of improved CVD prevention practice across the health and community sectors.

The aims of the MoFoP study are to: (1) test the feasibility of the *HeartLink* pilot processes including organizational readiness and resource implications for each key stakeholder group with regards to the implementation of the intervention; (2) measure the efficacy of the *HeartLink* pilot in six general practices in the Australian Capital Territory (ACT), Australia; and (3) identify the key elements of an effective model for the prevention of CVD in primary health care, and critical success factors for implementation and sustainability.

A mix of interrelating theoretical and framing approaches governing different aspects of the study have guided the study. For example, the trans-theoretical model of behavior (stages of change) informs individual behavior change [18], the normalization process theory relates to the implementation of the intervention [19], with the expanded chronic care model and complex adaptive systems approach providing overarching frameworks [14,20].

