### HeartLink Participant Eligibility and Recruitment

Inclusion and exclusion criteria for *HeartLink* were established. Patients needed to be 45-74 years old (35-74 years old for Aboriginal and/or Torres Strait Islander people), have a CVAR >15% over the next five years, and an absence of established CVD, diabetes, or a previous cardiovascular event
to be included. Patients were excluded if they had not attended the general practice in the last two years, had a complex coexisting medical condition or impairment, were non-English speaking, or were excluded from the intervention by their general practitioner.

The patients participating in the intervention will be recruited through their usual general practice. Each of the pilot general practices uses a clinical software program to manage patient information and possesses a clinical audit tool. The clinical audit tool has a CVD risk calculator report function that generates a list of patients (from the clinical software records) meeting the CVAR inclusion criterion of associated risk level. The CVAR calculator uses age, gender, systolic blood pressure, smoking status, and serum lipids to calculate risk. A history of left ventricular hypertrophy and having diabetes are also identified.

An initial list of patients with a CVAR > 15% will be generated for each practice, and from this list random subsamples in batches of around 20 patients (the actual number depending on practice size and available resource) will be generated at scheduled intervals. As each sample is identified, the invitation letters will be posted (with up to two reminders) to invite participants to attend their practice for a “heart and stroke check”. Those attending the practice for the check will be offered participation in a health behavior change program if they are eligible. The scheduled sampling will occur over a six month period until the target sample size is achieved. Figure 2 shows the *HeartLink* participant pathway.

The University of Canberra’s Human Research Ethics Committee approved this study (Project number 11-141).

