The GP consultation will comprise the usual care in relation to the management of the patient’s CVD risk profile, including making referrals to allied health professionals or medical specialists as required. GPs and practice nurses in participating practices will be offered professional development with regards to CVAR management guidelines, and will be provided with copies of the guidelines. After the GP consultation, the patient then returns to the practice nurse to consolidate the information provided by the GP. The patients will receive a brief intervention related to lifestyle modification and medication adherence, supported by Heart Foundation print material. The practice nurse consultation will be informed by the Health Change Australia (HCA) approach to health behavior change, and will aim to improve patient readiness for lifestyle change [27,28]. *HeartLink* uses the HCA approach across the intervention to provide patients with a consistent health behavior change paradigm, reinforced at each contact.

The eligible patients will then be offered participation in the health behavior change support program. If patients do not wish to progress to the program or are deemed by their GP to be ineligible, they will be given information on other health behavior change support options and offered ongoing usual care. The eligible patients who are initially not prepared to participate in the program will be provided with an opportunity to join the program at a later stage if they recontact their general practice within the recruitment timeframe of six months. The patients who are eligible and agree to participate in the health behavior change support program will be referred to the *HeartLink* Lifestyle Advisor linked to their practice.

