### Data Collection

#### Primary Health Outcome Measure

The primary health outcome measure for the study will be the change in the CVAR percentage score for the *HeartLink* intervention participants. A range of patient-reported health and well being outcomes will also be examined, including physical activity levels, fruit and vegetable intake, CVD medication adherence, health related quality of life, generalized self-efficacy, and intention to change key health behaviors related to CVD risk reduction.

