#### Individual Health and Well Being Data

Health related data will be collected from all *HeartLink* patients using validated tools via a paper-based survey administered at baseline and at 12 months. The survey will determine: (1) Physical activity levels, the usual physical activity levels will be collected via the Active Australia survey, which has been reported as reliable and having acceptable validity within an adult Australian population [30]. (2) Fruit and vegetable intake, the number of servings of fruit and vegetables will be assessed using validated questions from the National Nutrition Survey [31]. (3) Medication adherence, the participant’s adherence to the prescribed medication (antihypertensive and lipid lowering medication) is an important factor in reducing cardiovascular risk [32]. The participant’s adherence to CVD related medication (if medication has been prescribed) will be assessed using the four-item Morisky scale for each category of medication [33]. (4) Quality of life, the health related quality of life will be assessed using the short form (SF)-12v2 Health Survey (SF12 v2). The SF12 v2 is a validated and commonly used tool that provides insight into mental and physical functioning and overall health related quality of life [34]. (5) Generalized self-efficacy measure, a validated generalized self-efficacy measure, the General Self-Efficacy Scale will be used, as self-efficacy is an important determinant of behavior change. While a number of tools have been developed to measure self-efficacy in relation to specific health promoting behaviors, a generalized self-efficacy measure was selected, given that each patient will be choosing which particular health behavior or behaviors they are ready to change [35]. And (6) Intention for lifestyle change measure, several validated questions related to key lifestyle change measures for CVD risk reduction, such as dietary changes, alcohol intake, and smoking, and based on the transtheoretical model of behavior change will be included. The lifestyle change messages are all included in the Heart Foundation printed education material provided to each intervention participant [36].

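### Change in CVAR reflects the whole HeartLink package, including any drug treatment by the GP, so it is not an all-round measure and cannot by itself show which element worked

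*Protocol article*

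**What the plan says.** The section Primary Health Outcome Measure states: "The primary health outcome measure for the study will be the change in the CVAR percentage score for the" HeartLink participants. The section Quantitative Data Analysis gives the reason: "The CVAR was chosen as the primary health outcome, as it represents an all around measure of the" intervention's capacity to achieve what it set out to do.

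The section HeartLink Participant Eligibility and Recruitment lists what enters the score: "The CVAR calculator uses age, gender, systolic blood pressure, smoking status, and serum lipids to calculate risk".

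On the recall visit, the Enhanced Usual Care section says: "The GP consultation will comprise the usual care in relation to the management of the patient’s CVD risk profile". GPs and practice nurses "will be offered professional development with regards to CVAR management guidelines, and will be provided with copies of the guidelines". After the GP, the patient returns to the nurse for a brief intervention on lifestyle and medication adherence. Eligible patients who agree are then referred to a Lifestyle Advisor.

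The only medication measure described is adherence, which "if medication has been prescribed) will be assessed using the four-item Morisky scale for each category of medication" (Individual Health and Well Being Data).

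The third aim is to "identify the key elements of an effective model for the prevention of CVD in primary health care" (The Model for Prevention Study). The design is a single group without a control. The analysis described is a set of univariate pre/post comparisons: chi-square or Fisher's exact tests for proportions, t tests for normally distributed variables, and Wilcoxon signed rank tests otherwise.

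**The concern.** The outcome is presented as covering HeartLink's objectives as a whole, yet it registers only part of them. Lifestyle support and links between general practice and community services are central to the study's rationale. The score sees the first only at one remove and the second not at all. It does respond directly to blood pressure and lipids, which the GP may treat with drugs in the same pathway before the advisor is involved.

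The third aim is at stake. The section Qualitative Data Analysis says the integrated results will inform the implementation model. The pilot's effect size is also to feed the sample size of a later cluster randomized trial. If CVAR change is read as a general verdict on HeartLink, the article describes no quantitative result that would show whether medication, smoking or other lifestyle change lay behind it.

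The adherence outcome has a smaller, related problem. Adherence is scored only where a drug category has been prescribed. A patient with no prescription in that category at the baseline survey has no baseline score, so an unpaired comparison of proportions before and after can set different people against each other.

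**Working it through.** **Figure in the article.** The sample size is 6 practices x 30 patients = 180, which agrees with the stated total. The article gives no significance level, power, effect size or standard deviation (SD), so no other stated figure can be checked here.

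**Objectives against inputs.**
- Systolic pressure: a direct input; a target of antihypertensive drugs and open to diet and activity.
- Lipids: a direct input; a target of lipid-lowering drugs and open to diet and activity.
- Smoking status: a direct input and a lifestyle target.
- Fruit and vegetable intake and physical activity: not inputs; they act only through the items above.
- Linkage between general practice and community services: not an input.
- Age and gender: inputs that no part of HeartLink can change.

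Three inputs are therefore modifiable, and two of them are targets of the drug classes named in the adherence item. That item itself describes adherence to these drugs as important for lowering risk.

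**Can the described data separate the routes?** Blood pressure, total and HDL cholesterol, and smoking are recorded at baseline and 12 months, so a split by component is possible. The article mentions no record of drugs started or intensified, and no comparison that relates CVAR change to medication.

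**How large might a drug contribution be?** The article gives no inputs for this, so what follows is an illustration on assumed values only.

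Mean fall from drugs alone = baseline CVAR x share starting drugs x relative fall in CVAR among starters. Assume a baseline of 16% to 25%, a share of 20% to 60%, a relative fall of 10% to 30%, and no lifestyle effect.
- Low: 16 x 0.20 x 0.10 = 0.32 points.
- Middle: 20 x 0.40 x 0.20 = 1.6 points.
- High: 25 x 0.60 x 0.30 = 4.5 points.

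Power of a paired test at two-sided 5% = Phi(fall / (SD / sqrt(n)) - 1.96), with an assumed SD of change of 4 to 6 points.
- Middle, n = 180: SD 6 gives 1.6 / (6 / 13.42) - 1.96 = 1.62, power 0.95. SD 4 gives 5.37 - 1.96 = 3.41, power above 0.99.
- Middle, n = 60: power 0.54 (SD 6) to 0.87 (SD 4).
- Low, n = 180: power 0.11 (SD 6) to 0.19 (SD 4).

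A significant fall in CVAR could thus arise with no lifestyle or linkage effect. At the low end of the assumptions a drug effect alone would usually not reach significance.

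**Adherence comparison.** The chi-square test is described for pre and post groups and does not pair patients. With scores present only for those prescribed, its two groups need not be the same people. The Wilcoxon signed rank test is paired and uses only patients with both scores, so the problem arises when adherence is compared as a proportion.

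**The case against.** The strongest reply is that drug treatment lies inside the intervention. HeartLink is defined as enhanced usual care plus behaviour change support. Its aims include better clinical management of high-risk patients, GPs are offered guideline training, and the nurse's session covers medication adherence. For a combined package, a combined risk score is a defensible primary outcome. This stands: a drug-related fall is partly a legitimate HeartLink effect.

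A reader might infer more: that drugs are started at the recall visit and that the plan would credit their effect to the lifestyle and linkage model. The documents do not support that. The GP consultation is described as usual-care management of the risk profile, and the only action named is referral; prescribing at that visit is an inference. No section attributes a CVAR fall to lifestyle or linkage alone. Activity, diet, self-efficacy and intention are measured separately. Linkage is studied through interviews, advisor diaries and process audits, and the case study integrates these sources.

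A reader might also put a percentage on the drug share. On one set of assumptions (30% to 50% started or intensified, 4 points each, total fall 2 to 3 points), the share is 0.30 x 4 / 3 = 40% to 0.50 x 4 / 2 = 100%. Every input is assumed, and the upper value reaches 100% only because the chosen total equals the chosen drug effect. It is not evidence of size.

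It is also fair to say that a table by component or medication could sit in a fuller plan, and that the article calls the design preexperimental and looks to a later controlled trial. What remains is the stated justification, which the article's own list of inputs contradicts, and the absence of medication starts and changes from the data it describes.

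**Conclusion.** The point holds as one of interpretation, not of arithmetic. CVAR change is an acceptable outcome for the package, but it is not an all-round measure of HeartLink's objectives. It mixes medication and lifestyle, reaches diet and activity only through blood pressure, lipids and smoking, and does not register linkage. In a one-group design it cannot by itself identify the effective element, so it can serve the third aim only alongside other evidence.

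The size of any drug contribution cannot be derived from the documents. The 0.3 to 4.5 point range rests wholly on assumed baseline risk, share treated and relative effect. The conclusion about the outcome does not depend on those values; it follows from the list of inputs, the care pathway and the single-group design. The adherence point depends only on scores existing just for those prescribed and on the use of an unpaired test.

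**What to change.** 1. In Quantitative Data Analysis, replace the justification with a statement that CVAR change reflects medication and lifestyle combined and does not measure linkage.
2. Report CVAR change overall and split by systolic pressure, lipids and smoking, recomputing the score with one input changed at a time from the values already collected at baseline and 12 months. The parts need not add up to the total, and the table should say so.
3. Report CVAR change descriptively by whether antihypertensive or lipid-lowering medication was started or intensified between the two times, taken from the practice software. At a minimum, identify new starts from the Morisky categories that apply at each survey; this would miss intensification.
4. Limit the pre/post adherence comparison to patients prescribed that drug category at both times, analyse it as paired data, and state how many patients it covers.

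The cost is one extra data extract from software the practices already use, and one table. The article reports post-intervention data collection as still underway, so both are feasible. The downside is that the medication groups are defined after baseline: the results are descriptive, not causal, and will not settle which element worked. None of this alters patient management.

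### The tests named for counts and percentages ignore both stage order and within-patient pairing; stage-of-change items, if analyzed that way, would lose much of their power

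*Protocol article*

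**What the plan says.** The Quantitative Data Analysis section sets three rules for the clinical and survey data.

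- **Counts and percentages:** "Univariate comparisons between the pre and post intervention groups will be conducted using a chi-square test for equal proportion". Fisher's test is the small-sample alternative: "exact tests where numbers are small), and reported as numbers and percentages".
- **Continuous, normally distributed variables:** Student's t tests.
- **The remainder:** "Nonnormally distributed data will be compared using Wilcoxon signed rank tests".

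The section does not link any of the three rules to a particular survey item.

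Under Individual Health and Well Being Data, the intention-to-change measure is several questions "based on the transtheoretical model of behavior change will be included". The section The Model for Prevention Study describes that model as stages: "the trans-theoretical model of behavior (stages of change) informs individual behavior change". The number of answer categories and the scoring are not given. Medication adherence "will be assessed using the four-item Morisky scale for each category of medication". All survey measures are collected "via a paper-based survey administered at baseline and at 12 months", in a one-group pre/post design.

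The primary health outcome is the change in cardiovascular absolute risk (CVAR). Intention and adherence are among the other patient-reported outcomes.

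**The concern.** Stages of change have a direction, and each patient supplies a stage at both time points. A chi-square or Fisher test on pre and post counts uses neither fact. It returns the same p-value if the stages are relabeled in any order, and it treats 180 patients measured twice as 360 unrelated people.

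The second property matters more than it may seem. Most patients stay at or near their starting stage, so the pre and post counts are positively correlated. A test that assumes independence then overstates the variance of the difference, and it rejects far less often than its nominal 5% when nothing has changed.

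The practice nurse consultation aims to improve readiness for lifestyle change, so movement through the stages is a close measure of what the intervention acts on. The pilot is also meant to inform a larger cluster randomized trial. A null result from an insensitive test could be carried into that design as a lack of behavioral response.

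**Working it through.** **The plan's own figure.** 30 patients × 6 practices = 180. The article gives no alpha, power, effect size or standard deviation for any outcome, so there is no power calculation to reproduce. All power figures below rest on assumptions that the article does not supply.

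**Four tests, to separate the two faults** (two-sided 0.05):

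| Test | Paired | Uses order |
|---|---|---|
| Chi-square on pre/post counts (named) | no | no |
| Rank-sum | no | yes |
| Stuart-Maxwell | yes | no |
| Wilcoxon signed rank (named) | yes | yes |

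**Model A: latent shift.** Each patient has two standard normal scores with correlation 0.6. The 12-month score is raised by the shift, and both are cut at equal baseline quantiles into stages. Repeated runs agree to within about 2 points.

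| Stages, pairs, shift | Chi-square | Rank-sum | Stuart-Maxwell | Signed rank |
|---|---|---|---|---|
| 5, 90, 0.3 SD | about 0.20 | about 0.45 | about 0.54 | about 0.77 |
| 5, 180, 0.2 SD | about 0.16 | about 0.40 | about 0.53 | about 0.75 |
| 3, 90, 0.3 SD | 0.27 | 0.40 | 0.59 | 0.71 |

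With 5 stages and 90 pairs:
- Pairing alone adds 0.54 − 0.20 = 0.34.
- Order then adds 0.77 − 0.54 = 0.23.

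With 3 stages, the order gain after pairing is 0.71 − 0.59 = 0.12, roughly 10 points. With no shift and 90 pairs, both paired tests reject about 5% of the time; chi-square rejects about 2%.

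**Model B: one-step moves.** 25% of patients would move up one stage and 10% down one, with no move beyond the end stages; 180 pairs.

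| Baseline | Chi-square | Rank-sum | Stuart-Maxwell | Signed rank | Order gain once paired |
|---|---|---|---|---|---|
| 5 stages, uniform | 0.00 | 0.00 | 0.66 | 0.86 | 0.20 |
| 5, early-weighted | 0.00 | 0.01 | 0.92 | 0.99 | 0.07 |
| 5, mid-weighted | 0.01 | 0.00 | 0.81 | 0.91 | 0.10 |
| 5, late-weighted | 0.00 | 0.00 | 0.31 | 0.50 | 0.19 |
| 3 stages, uniform | 0.01 | 0.02 | 0.68 | 0.78 | 0.10 |

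Here an ordered but unpaired test repairs almost nothing. Pairing does most of the work, and order adds 0.07 to 0.20. For larger movement (45% up, 10% down, mid-weighted), order helps even without pairing: 0.28 for chi-square, 0.78 for rank-sum.

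**Degrees of freedom.** An effect that lies wholly in the ordered direction and has 80% power on 1 df (non-centrality 7.85) has power 0.71 on 2 df, 0.64 on 3 df and 0.60 on 4 df. This is the most favorable case for an ordered test. If an item is collapsed to two categories there is 1 df and no order left to lose; only the pairing fault remains.

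**Precision of the proposed summary.** Let a and f be the observed proportions who advanced and fell back. The difference is a − f, with SE = √{[a + f − (a − f)²]/n}. For a = 0.25, f = 0.10, n = 180: SE = √[(0.35 − 0.0225)/180] = 0.043, so the difference is 0.15 with a 95% confidence interval of about 0.07 to 0.23.

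**The case against.** The strongest reply is that the article never sends the stage items to chi-square. Its wording is a general list of tests, and matching tests to secondary items is normally left to an analysis plan. A scored stage item could fall under the Wilcoxon sentence, which is not confined to continuous variables. That stands. A reader might infer that the plan has fixed chi-square for these items, but the text supports only a conditional statement. What remains is that the rule for counts and percentages is stated by name, that stage data are naturally presented in that form, and that neither test it offers suits repeated measurements on the same patients.

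Four other stronger readings also fail:

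- **Order as the main cause.** A reader might blame the low power chiefly on ignoring order. The simulations show that much of the loss, and in Model B most of it, comes from ignoring pairing.
- **Five stages and four degrees of freedom as facts.** The article gives no number of categories. With fewer categories the order gain shrinks.
- **A significant result would hide direction.** Results are to be reported as numbers and percentages, so the two distributions would show the net direction. They would not show how many individuals advanced and how many fell back.
- **Adherence is wrongly analyzed.** A four-item scale score already fits the Wilcoxon sentence. It needs confirmation, not correction.

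It is also fair that this is a pilot, that the outcome is not primary, and that interviews and focus groups give further evidence on behavioral response.

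**Conclusion.** The point holds conditionally and is minor. If stage-of-change counts are compared by the rule the article gives for counts and percentages, the test is both unordered and unpaired. Its power is then about 0.20 where the signed rank test has about 0.77 (5 equally frequent stages, latent correlation 0.6, 90 pairs, 0.3 SD shift). Once pairing is respected, order is worth about 10 to 23 points under the latent-shift model and 7 to 20 points under one-step moves at 180 pairs.

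The number of stages, baseline distribution, correlation, shift, alpha and number of complete pairs (other than the planned 180) are all assumptions. The direction of the result does not depend on them as long as the items keep three or more ordered categories. The primary CVAR analysis is unaffected.

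**What to change.** Add to Quantitative Data Analysis:

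1. Stage-of-change items kept as ordered stages are analyzed by the Wilcoxon signed rank test already named there, applied to each patient's change from baseline to 12 months.
2. For each such item, report the percentage of patients who advanced at least one stage minus the percentage who fell back, with a 95% confidence interval.
3. Items collapsed to two categories are compared by a paired test of proportions (McNemar), not chi-square or Fisher.
4. Confirm that the four-item adherence score falls under the same Wilcoxon rule.

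The cost is a few sentences. No further data are needed, because both surveys come from the same patients; their answers need only be linked across the two time points. McNemar is the only test not already in the section.
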